# **Selection and Withdrawal of Subjects**

## **Inclusion Criteria**

Inclusion criteria for participants taking part in this study include:

(a) 18+ years,

(b) from a refugee background,

(c) able to speak and read Farsi, and

(d) experiencing elevated levels of psychological distress (K10 > 19.9)

## **Exclusion Criteria**

Exclusion criteria for those who are not eligible to participate in the study include:

(a) participants that do not meet the above inclusion criteria

(b) acute medical conditions,

(c) imminent suicide risk or with expressed acute needs/protection risks (e.g., a woman who reports that she is at acute risk of domestic and/or sexual

violence),

(d) severe mental disorder (psychotic disorders, substance-dependence),

(e) severe cognitive impairment (e.g., severe intellectual disability or dementia), and/or

(f) concurrent psychological treatment (e.g., currently receiving psychological services from a psychologist, counsellor or mental health-focused program)

(g) no access to a smart phone and internet connection.

## **Recruitment Strategy**

The research team will periodically post a study advertisement on our social media accounts (Pathways to Refugee Wellbeing WhatsApp and Instagram accounts). This method of recruitment has previously been used by the research team to recruit 1,235 refugees living in Indonesia for a longitudinal online study (HC190494). Additionally, the study advertisement will be sent (via a WhatsApp message) to refugee participants from our previous research project in Indonesia (HC190494) who gave permission to be contacted about future research studies.

The recruitment ad will direct potential participants to a 5-minute online screener form where interested participants can read further information on the program and decide whether they wish to provide consent to complete the screener form.

## **Screening**

Screening will be conducted in two stages (see Figure below titled, “Schematic of Screening Process and Trial Stages”). First, a brief online screening form will be used to assess inclusion criteria. Second, those who meet the inclusion criteria will then be screened over-the-phone by a trained assessor to verify their responses and additionally assess exclusion criteria.

(a) Online Screener

Potential participants who follow the link in the study advertisement will be directed to a brief online screener form on Qualtrics. The first section of this form is the Participant Information Statement and Consent Form that outlines the two-stage screening process. Potential participants can then indicate if they consent to proceed to the screener. Following informed consent, potential participants will be directed to complete brief questions to verify demographic eligibility (i.e., to verify that they are an adult, Farsi-speaking refugee residing in the Greater Jakarta region of Indonesia). The presence of at least moderate levels of psychological distress will be screened using the Kessler Psychological Distress Scale (K-10; Kessler et al., 2002), where a score above 19.9 will be required to be eligible. (This scale is outlined in *10.1 Trial Intervention*.) Ineligible participants (i.e., those who provided responses that indicate that they do not meet the inclusion criteria) will be advised of their ineligibility immediately within the Qualtrics screener survey or, in any cases where their eligibility needs to be discussed or verified by the team, via email/WhatsApp shortly thereafter. For example, if participants are not eligible for the trial because they are too young or are not from the target language group, they will be provided with feedback explaining why they are not eligible for the study and, where relevant, alternate referral information may be provided. Similarly, if participants are not selected for the trial because they score below the cut-off scores for the K-10, they will be provided feedback on their test outcome and it will be explained why they are not eligible for the study. These feedback scripts have been adapted from the manuals provided by the World Health Orgainsation (see pp. 88-89 of the PM+ intervention manual; WHO, 2016).

(b) Phone Screener

Participants who meet inclusion criteria according to the online screener will then be contacted by a trained assessor for a follow-up phone screener call to verify their eligibility (and assess exclusion criteria). Data collected during the screening call will be recorded by the assessor using Qualtrics.

Individuals who meet the exclusion criteria as described in *9.2 Exclusion Criteria* will be excluded and referred externally for appropriate treatment and support. This refers to individuals with imminent suicide risk or with expressed acute needs/protection risks (for example, a woman who expresses that she is at acute risk of domestic violence or sexual assault). Suicidal ideation will be explored through the ‘assessment of thoughts of suicide’ tool developed by the World Health Organisation (WHO, 2016, pp86). In addition, we will also exclude individuals with severe mental disorder (psychotic disorders, substance-dependence) or severe cognitive impairment (e.g., severe intellectual disability or dementia). Mental, neurological or substance use disorders will be screened with the ‘impairments possibly due to severe mental, neurological or substance use disorders’ tool of the Problem Management Plus (PM+) intervention manual (WHO, 2016, pp87). Individuals meeting the exclusion criteria will be provided with referral information for relevant specialist support hotline and crisis services (UNHCR or Church World Service). If a participant meets any exclusion criteria, they will be immediately notified by the assessor using feedback scripts that have been adapted from the manuals provided by the World Health Orgainsation (see pp. 88-89 of the PM+ intervention manual; WHO, 2016).

Participants that do not endorse any exclusion criteria will be informed of their eligibility for the trial and sent an email/WhatsApp message with a Qualtrics link to the Participant Information Statement and Consent form for the intervention trial. Participants who provide informed consent will then be contacted by the research team to schedule their first assessment.

**Schematic of Screening Process and Trial Stages**

**
[figure not shown]
**

## **Consent**

Consent will be obtained in a two stage-process: (1) informed consent for screening, and (2) informed consent for the DWM intervention.

First, consent for the screening process (i.e., online form and, if eligible, follow-up screener call) will be obtained at the beginning of the online screener form. Participants will be directed to the online screener by following the link in the Study Advertisement/Recruitment Ad. The beginning of the online screener will be a brief overview of the research project, followed by the PICF1(Screener) – Easy Read. Participants will be asked to read the consent form. They will have sufficient time to consider their participation as this is an online form, completed without the presence of researchers and in the participant’s own time. Participants will be advised to contact the research team if they have questions. Once they are comfortable providing their consent to participate, they will be asked to provide consent by clicking the relevant checkbox in the online form, after which, they will complete the online screener. If a participant declines to consent, they will not be contacted about the research study. In the event that potentially interested participants contact the team directly to ask questions and/or express their interest in participating, the researcher, once answering their questions, will either re-direct them to the online screener or, if time permitting, administer the screener questions verbally. In the event of verbal screening, real or perceived coercion will be avoided because the research member will make it explicit that participation in the screener is voluntary, and that declining to participate will not affect the participant’s relationship with UNSW. Participants will be provided with the opportunity to ask further questions before consenting. If participants decline consent to screening, they will not be contacted.

Second, participants who are assessed as eligible, following the online and/or phone screening process, will be sent an email/WhatsApp message with a link to the PICF2(Intervention) – Easy Read. Participants will be asked to read the consent form. They will have sufficient time to consider their participation as this is an online consent form, completed without the presence of researchers and in the participant’s own time. Participants will be advised to contact the research team if they have questions. If they wish to consent to participation in the trial, they can provide consent by clicking the relevant checkbox in the online form. Participants who provide consent will then be contacted by the research team to book their first Structured Assessment to commence participation.

This written consent process is appropriate for the data collection method and participant group because potential participants will have ample time to consider their participation in this study, all information about the study will be presented in Farsi (the participants’ own language), and if participants have any queries, they are able to contact the research team.

## **Withdrawal of Consent or Participant**

**Withdrawal of Individual Subjects**

Subjects can leave the study at any time for any reason if they wish to do so without any consequences. The investigator can decide to withdraw a subject from the study for urgent medical reasons, protection needs or resettlement changes.

- Specific criteria for withdrawal (if applicable): Not applicable for this study.
- Replacement of individual subjects after withdrawal: No new subjects will be included for each withdrawn subject.
- Follow-up of subjects withdrawn from treatment: If a subject decides to withdraw from the study, the investigator will ask for the reason. It will be enquired whether the subject wishes to withdraw from the entire study or from a specific time point only, to determine whether the subject wishes to be re-contacted at a later time.

# **Treatment** **of Subjects**

The DWM Intervention Program

DWM is a brief, remotely delivered, self-help intervention (see Doing what matters in times of stress: an illustrated guide. Geneva: World Health Organization; 2020 (<https://www.who.int/publications-detail-redirect/9789240003927> ). It is an illustrated guide of an existing intervention called Self-Help Plus (SH+) (Epping-Jordan et al., 2016). The DWM manual was released by the WHO in 2020 to support the remote delivery of SH+, considering the COVID-19 pandemic and a growing need for online/remotely delivered interventions. DWM is:

- based on acceptance and commitment therapy and adapted for many settings;
- intended as an intervention for managing stress and coping with adversity;
- relevant for anyone above the age of 18;
- designed to be completed over a short period of time;
- practical so that participants can practise skills regularly on their own; and
- illustrated, with accompanying audio recordings to support regular practice.

DWM can be delivered as either a guided or unguided intervention. For the current project, we are testing the guided version of DWM. This means that participants in the active treatment condition will receive a copy of the DWM illustrated workbook that contains five ‘lessons’. This workbook will be accompanied by audio files that provide guided scripts for practicing the newly learnt techniques. Finally, participants will also receive five weekly calls from a trained facilitator, who will help participants to learn and practice the therapeutic techniques. This delivery format is empirically supported by meta-analyses on the therapeutic effects of bibliotherapy, prerecorded self-help interventions, and guided self-help interventions (Cuijper, Munoz, Clarke & Lewinson, 2009; Cuijpers, Donker, van Straten & Andersson, 2010). Participants in the waitlist control condition will gain access to the unguided version of DWM (i.e., workbook and audio files) upon completion of their final assessment at the end of the 9-week waitlist period.

The DWM program is based on Acceptance and Commitment Therapy (ACT; Hayes et al., 2013) techniques that are empirically supported (Hacker, Stone & MacBeth, 2016) and formally recommended by the WHO. The manual involves the following empirically supported elements: psychoeducation, grounding, cognitive defusion, mindfulness exercises, values clarification, and compassion exercises. There is substantial evidence linking ACT-based interventions to reductions in anxiety, depression and stress (Hacker et al., 2016; French, Golijani-Moghaddam & Schroder, 2017).

DWM Skills and Modules

DWM seeks to reduce psychological symptoms by introducing stress management techniques. It comprises five weekly modules, each focused on a specific skill (see Table 1). The specific skill is first learnt via the DWM illustrated workbook and accompanying audio file(s), and then practiced and reinforced by the weekly session with a trained facilitator.

*Table 1. Overview of DWM Modules*

| **Lesson (Overall Theme)** | **Main Goal(s)** | **Core technique(s)** |
| --- | --- | --- |
| 1 (Grounding) | - Practice present-centered awareness during an everyday activity - Practice grounding, to respond effectively to stress | - Psychoeducation - Grounding/Contact with the present moment |
| 2 (Unhooking) | - Practice noticing and naming difficult thoughts and feelings - Refocus on the present | - Grounding/Contact with the present moment - Acceptance - Defusion |
| 3 (Values) | - Identify personal values - Learn to engage in values-guided actions | - Values - Committed Action |
| 4 (Being Kind) | - Enhance kindness to yourself and others | - Compassion towards self and others |
| 5 (Making Room) | - Learn how to accept/tolerate difficult thoughts and feelings via compassion | - Acceptance - Defusion |

The Control Condition

Participants in the Waitlist Control condition will participate in repeated assessments (mid-treatment, post-treatment and follow-up assessments) over a 9-week waitlist period. Following completion of the final assessment, participants will be receive a link to the DWM workbook and audio files.

Use of Co-Intervention (if applicable): Participants are allowed to use any existing prescribed medication or routine care related to any co-morbid health conditions.

- 1. **Trial Intervention**

This trial will be carried out in the Greater Jakarta area of Indonesia. The study will be advertised via the research team’s existing social media channels and participant database. Interested participants will be able to complete an online screener form, which outlines the screening and consent process. Participants who consent to the screener will complete brief questions designed to assess inclusion criteria. Eligible participants will be adult refugees from Farsi-speaking backgrounds who reside in the Greater Jakarta area and score above 19.9 on the K-10. Individuals screened by the online form as potentially eligible will then be contacted by a trained research team member to assess exclusion criteria. Individuals with acute needs, such as imminent suicide or protection risks, will be excluded and referred for appropriate treatment and support. In addition, we will also exclude individuals with severe mental disorders (psychotic disorders, substance-dependence) or severe cognitive impairment (e.g., severe intellectual disability or dementia). We will screen for these exclusion criteria using the tools developed by the World Health Organisation and outlined in their Problem Management Plus (PM+) intervention manual (WHO, 2016, pp. 86-87). Individuals meeting the exclusion criteria will be referred to UNHCR (Jakarta Office) or Church World Service, or to local social service provision, depending on their needs. If the participant agrees, the assessment results will be provided to the referring organisation with permission of the participant and the research team.

Participants deemed eligible based on the online screener and phone screener process will be invited to participate in the trial and sent a link to review the trial’s Participant Information Statement and Consent Form. Following informed consent, participants will be contacted to book their first assessment (Structured Assessment 1). Structured Assessments will be conducted by trained research assistants called ‘Assessors’ (see ‘Trial Personnel’ below) and will involve the administration of the scales in a structured interview format to assess mental health and psychosocial functioning (see ‘Measurement Instruments’ below). If, at the time of the baseline assessment (Structured Assessment 1), the participant’s symptoms of psychological distress have spontaneously improved such that they no longer score above the cut-off, they will be provided feedback on their test outcomes and it will be explained why they are no longer eligible for the study.

After the baseline assessment, participants will be randomized on a 2:1 (active treatment : waitlist control) basis by an independent research assistant, not involved in the assessments, using computerized software. Participants will be randomised to either the Active Treatment condition (*n*=214) or the Waitlist Control condition (*n*=107) to form a single-blind waitlist control RCT design. Participants in the Active Treatment condition will receive the 5-week DWM intervention from Weeks 1-5. Regardless of condition, all participants will complete Structured Assessments every 3 weeks.Upon completion of the final Structured Assessment (1-month follow-up, conducted 9-weeks following baseline assessment), participants in the Waitlist Control condition will gain access to the DWM workbook and audio files.

The instruments administered in Structured Assessments 2-4 closely resemble those used in Structured Assessment 1, with minor changes (as some scales do not need to be re-administered). This is outlined in the ‘Measurement Instruments’ section below. In case participants do not attend a scheduled assessment, the research team will attempt to contact them via follow-up text messages and/or phone calls for a maximum of eight times for scheduling a new appointment.

Participants in both conditions will also complete two 1-week ecological momentary assessment (EMA) blocks, initiated the day following pre-treatment assessment and again following post-treatment assessment (in week 6). At the end of Structured Assessment 1 (pre-treatment), assessors will explain the EMA process and guide participants in downloading and setting-up the Avicenna application on their smart phone. The participant and assessor will then complete a practice survey together. The next day, the participant’s 7-day block will commence. At five random times between 10am and 10pm each day, participants will receive notifications to complete a 1-2 minute survey on their phone. This procedure will be repeated in week 6, following the completion of Structured Assessment 3 (post-treatment). During an EMA block, if participants miss 2 or more of the 5 daily surveys, they will be contacted (either via text message or call) to check whether the participant is experiencing any issues (such as technological difficulties) that the team can assist with to support full participation.

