# **Sample Size**

We plan to enrol 303 participants into the trial. As a key focus of this study is to investigate psychological and social mechanisms underlying the impact of DWM on mental health outcomes, we will implement a 2:1 allocation ratio (DWM to WLC) to ensure analyses are adequately powered. Based on previous research, we aim to detect a medium between-groups effect size (0.40) (Tol et al., 2020; Acarturk et al., 2020) on our main outcome measure (Kessler-10). With alpha of 0.05 and power of 80%, we will need to include a minimum of 224 participants across both arms (150 in the DWM arm and 73 in the WLC). We estimate 35% attrition given the mobile nature of the refugee population in Indonesia, and thus we will need to recruit 303 participants into the trial.

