**Trial Personnel:**

Facilitators will be responsible for conducting weekly DWM sessions with participants, via Zoom or phone calls. Facilitators are bilingual (English/Farsi) speakers with prior experience working with people from refugee backgrounds in Indonesia (e.g., previously working as teachers at refugee learning centers, staff in refugee-led originisations and/or interpreters for refugee-focused NGOs in Indonesia). Facilitators will receive 28 hours of in-person training by the research team. The in-person training covers: the DWM manual and techniques, general counselling/facilitation techniques, and responding to participant distress. Ongoing monitoring of facilitators’ capacity to practice will be conducted through regular supervision by a member of the research team who is a Clinical Psychologist. This oversight will help to ensure that any potential concerns about the capacity of the facilitators to carry out their roles is identified and addressed. Protocol adherence will be ensured by regular supervision of the facilitators and treatment fidelity checks using a checklist.

Assessors will be responsible for conducting the Structured Assessments with participants, via Zoom or phone calls. Assessors are bilingual (English/Farsi) speakers with prior experience working with people from refugee backgrounds in Indonesian (e.g., previously working as teachers at refugee learning centers, staff in refugee-led organisations and/or interpreters for refugee-focused NGOs in Indonesia). Assessors will receive 28 hours of in-person training by the research team. The in-person training covers: administering the instruments, general interview techniques, and responding to participant distress. Ongoing monitoring of assessors’ capacity to practice will be conducted through regular supervision by a member of the research team who is a Clinical Psychologist. This oversight will help to ensure that any potential concerns about the capacity of the assessors to carry out their roles is identified and addressed. Protocol adherence will be ensured by regular assessment fidelity checks using a checklist.

Supervisors are responsible for supervising the facilitators and assessors in the day-to-day running of the trial. Supervisors will hold at least Masters-level qualifications in Clinical Psychology.

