**Measurement Instruments:**

The instruments used to assess and monitor mental health and psychosocial functioning are outlined in the below table.

|  | **When measure is administered** | | | | |
| --- | --- | --- | --- | --- | --- |
| **Construct & Measure** | **Screener** | **Structured Assessment 1** | **Structured Assessments 2-4** | **Ecological Momentary Assessment** | **DWM sessions** |
| Demographics | X | X |  |  |  |
| Psychological Distress (K10)* | X | X | X |  |  |
| Posttraumatic Stress Reactions (PCL-6) |  | X | X |  |  |
| Suicidal Ideation (SIDAS) |  | X | X |  |  |
| Self-Identified Problems (PSYCHLOPS) |  | X | X |  |  |
| Wellbeing (WHO-5) |  | X | X |  |  |
| Psychological Flexibility (adapted CompACT & AAQ-II) |  | X | X |  |  |
| Repetitive Negative Thinking (PTQ- Short form) |  | X | X |  |  |
| Intolerance of Uncertainty (abbreviated IoUS) |  | X | X |  |  |
| Social Satisfaction and Functioning (abbreviated WHOQoL-BREF items and SAS-SR-modified) |  | X | X |  |  |
| Physical Health (abbreviated WHOQoL-BREF) |  | X | X |  |  |
| Post-Migration Living Difficulties (adapted PMLD Checklist) |  | X | X |  |  |
| Perceived benefit (newly adapted items) |  |  |  | X |  |
| Adverse Life Events (adapted HTQ) |  | X |  |  |  |
| Digital Markers** |  | X | X |  |  |
| Momentary Emotions and Stressors |  |  |  | X |  |
| Emotion Regulation Strategies (RESS-EMA) |  |  |  | X |  |
| Treatment fidelity (checklists) |  |  |  |  | X |
| Treatment contamination check |  | X | X | X |  |

*Psychological Distress (K10) is the primary outcome measure

**Digital Markers are measured in Structured Assessments 1 and 3 only.

*Screener and Primary Outcome Measure*

*Psychological Distress*

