Psychological distress will be measured through the Kessler-10 Psychological Distress Scale (Kessler et al., 2002). Ten items related to distress are rated on a five-point Likert scale. The sum of the ten items gives a total score ranging from 10 to 50. In a study among Kurdish and Afghan (former) refugees and asylum seekers in New Zealand and Australia, the following cut-off scores were used: 10-15.9 (*low risk of psychological distress*), 16-21.9 (*moderate levels of distress consistent with a diagnosis of moderate depression and/or anxiety disorder*), 22-29.9 (*high level of distress*) and 30 or more (*possibility of very high or severe levels of distress*) (Sulaiman-Hill & Thompson, 2010). In the current study, we will use a score of >19.9 as an indication of moderate to high levels of psychological distress. The K10 was found to be an accurate screener for common mental disorders cross-culturally (Patel et al., 2008; Fassaert et al., 2009, Sulaiman-Hill & Thompson, 2010, Tol et al., 2020). Furthermore, the K10 strongly correlated with other validated measures for screening for common mental disorders in primary care patients in India (*r*=.68 with GHQ-12 and *r*=.84 with SRQ, respectively) (Patel et al., 2008).

*Secondary Outcome Measures*

*PTSD symptoms*

Posttraumatic stress disorder (PTSD) symptoms during the past week according to a DSM-5 PTSD diagnosis will be measured using the PTSD Checklist for DSM-5, 6-item version (Weathers et al., 2013). Items are rated on a 0-4 scale and are summed to calculate a total severity score, with higher scores indicating worse symptomatology. This measure has previously been used with refugees (Tol et al., 2020).

*Suicidal Ideation*

The Suicidal Ideation Attributes Scale (SIDAS; Van Spijker et al., 2014) will be used to measure the presence and inference of suicidal thoughts over the past week. The scale has 5 items, each rated on a 0-10 scale. Scores are summed to calculate a total severity score, with high scores indicating worse symptomatology. However, if a participant scores zero on the first item, then items 2-4 are not administered.

*Self-identified Problems*

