# **Statistics**

Data collected throughout the study will be analysed using hierarchical linear modelling or linear mixed models. Both intention-to-treat analysis (ITT; using all randomised participants) and completers’ (PP) analysis will be used.

Primary study parameters:

The main conclusion for study aim 1 (testing the efficacy of the DWM intervention, according to K10 scores) will be based on the ITT analysis of the primary outcome. A secondary analysis of the primary outcome will also be presented using the PP population. To estimate the treatment effect, data from Structured Assessments 1-4 will be used. A linear mixed model will be employed for the primary endpoint analysis, which will have treatment as fixed effects, baseline measurement of primary endpoint as covariate, and subject as random effects. The mean difference between two treatment arms at each visit/time together with its 95% confidence interval will be derived from the mixed model. Covariate-adjusted mixed model of primary endpoint will also be performed by adding pre-specified covariates at baseline (gender, age, education, traumatic experiences, and severity of symptoms) into the above model.

- Secondary study parameters: A linear mixed model as mentioned for the primary outcome analysis will be carried out for analysing the secondary outcomes (e.g., PTSD, Suicidal Ideation, Self-Identified Problems, Wellbeing, Functional Impairment, Digital Markers).

The main conclusion for study aim 2 (testing the mechanisms of change within the DWM intervention) will be based on the PP analysis, to ensure that only data from participants who received a sufficient ‘dose’ of the intervention are analysed. Cross-lagged panel analysis will be used to determine the temporal sequencing of psychological factors over the course of the intervention period, to test whether the hypothesised processes were mechanisms of change driving the intervention effects [hypothesis 2].

- The hypothesised mechanisms are: psychological flexibility (primary), emotion regulation, social satisfaction and functioning, and intolerance of uncertainty.

Missing data: Missing data will be treated as missing at random (MAR). No imputations of missing values will be made, as multilevel models can deal with missing data (Singer & Willett, 2003).

Other study parameters:

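### The only stated remedy for a missed assessment is to rebook the full interview; a K10-only phone call by a blinded assessor would save some primary outcomes at little cost

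*Protocol*

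**What the plan says.** Section 10.1 (Trial Intervention) gives one procedure for a missed Structured Assessment: the team "will attempt to contact them via follow-up text messages and/or phone calls for a maximum of eight times for scheduling a new appointment". It describes the assessment as one that "will involve the administration of the scales in a structured interview format to assess mental health and psychosocial functioning", and says Assessments 2–4 closely resemble the first. Trial Personnel gives the channel: "Assessors will be responsible for conducting the Structured Assessments with participants, via Zoom or phone calls".

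Under Measurement Instruments, "Psychological Distress (K10) is the primary outcome measure", and the scale is short: "Ten items related to distress are rated on a five-point Likert scale". The K10 also forms part of the self-completed screening, done on "a brief online screener form on Qualtrics" (section 9.4).

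Section 8 states: "We estimate 35% attrition given the mobile nature of the refugee population in Indonesia". Section 14 treats missing data as missing at random and adds: "No imputations of missing values will be made". Section 9.6 allows a participant to drop out of a single time point, but names no minimum data set to offer that person.

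**The concern.** The stated contacts have a single aim, to book another interview. A participant who answers but will not sit through the whole battery is recorded as missing for that visit, and the primary outcome goes with the rest. Nothing in the design requires this. Ten items can be read over the phone by the same blinded assessor, in the same mode as the planned interview, during a contact the team is already making.

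What is at stake is the amount of missing primary data and the dependence on the missing-at-random assumption, which the observed data cannot verify. A participant who stops attending because distress has worsened, or has eased, is the case that could break that assumption. An observed K10 from such a person is worth more than any model-based substitute. How a missed visit is followed up is a matter of data collection, and the protocol fixes it in section 10.1.

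**Working it through.** **1. How much of the interview the K10 takes up.** Item counts are from Measurement Instruments, for scales scheduled at Assessments 2–4: K10 10, PCL 6, SIDAS 5 (fewer if the first item is zero), PSYCHLOPS 2, WHO-5 5, CompACT 10, AAQ-II 7, PTQ 9, intolerance of uncertainty 6, social satisfaction 2, SAS-SR 9, physical health 2, post-migration difficulties 17.

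The sum is 10+6+5+2+5+10+7+9+6+2+9+2+17 = 90, so the K10 is 10 of 90 items. The 12-item WHODAS is described but does not appear in the schedule table; including it gives 102. Assessment 3 adds two one-minute recorded speech prompts. The protocol gives no interview duration, so item count is the only documented measure of burden.

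**2. The protocol's sample size, reproduced.** Inputs from section 8: standardised difference 0.40, alpha 0.05 (two-sided assumed), power 80%, allocation 2:1.

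Control n = 1.5 × ((1.960 + 0.842)/0.40)² = 73.6, rounded up to 74, so the total is 222. A t-test calculation gives 222.7. The stated minimum of 224 is reproduced closely enough.

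**3. Where the shortfall comes from.** The recruitment target of 303 is 224 × 1.35 = 302.4, rounded up. Losing 35% of 303 leaves 303 × 0.65 = 197. Inflation by division gives 224/0.65 = 344.6, or 345, and 345 × 0.65 = 224. The gap between 197 and 224 is thus mainly an inflation error, a separate matter. Section 10.1 also gives 214 + 107 = 321 randomised, and 321 × 0.65 = 209.

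**4. Illustrative effect of recovering some K10s.** Let q be the share of missing K10s recovered.

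Evaluable N = N randomised × (1 − 0.35 × (1 − q)).

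Power = Φ(0.40 × √(2N/9) − 1.960), where 2N/9 is n₁n₂/(n₁+n₂) at 2:1.

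For N = 197: 0.40 × √43.8 = 2.646; 2.646 − 1.960 = 0.686; Φ(0.686) = 75.4%.

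| Recovered (q) | 303 randomised: N, power | 321 randomised: N, power |
|---|---|---|
| 0% | 197, 75.4% | 209, 77.8% |
| 10% | 208, 77.5% | 220, 79.9% |
| 20% | 218, 79.5% | 231, 81.8% |
| 25% | 223, 80.5% | 237, 82.7% |

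The t-test version is about 0.4 points lower where both were computed: 75.0% at 197 and 77.4% at 209.

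Reaching 224 needs 27 of the 106 missing values with 303 randomised (25.5%), or 15.35/112.35 = 13.7% with 321.

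**5. What limits q.** q is the share of missing participants who are reachable but unwilling, multiplied by the share of those who accept a short call. The protocol gives neither. Even if every such participant accepted, q = 25% would require at least a quarter of all missing participants to be reachable decliners.

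**The case against.** **The protocol does not forbid a K10-only contact.** True. It states one route and is silent on others, and an assessor manual not shown here might add a shorter one. A reader might infer that the K10 may be collected only with the full battery; the text does not say so. What stands is that the stated purpose of the contacts is rebooking. Improvised short calls would vary between assessors and have no agreed place in the primary analysis.

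**Burden is not the documented cause of loss.** Section 8 attributes attrition to mobility, and section 9.6 lists resettlement changes as a reason for withdrawal. Interviews are already remote, with up to eight contacts, so many of those still missing may be out of reach. This stands, and it is why the size of the benefit cannot be stated.

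**The power figures overstate the loss.** Also largely right. The baseline-adjusted mixed model in section 14 uses all assessments, so a participant who misses one visit still contributes the others. Baseline adjustment may raise power further: if 0.40 is in raw standard-deviation units and the baseline correlation is assumed to be 0.3, 0.4 or 0.5, N = 197 gives about 79%, 82% or 86%. The absence of imputation is not a defect in itself, since a likelihood-based mixed model under missing at random does not need it.

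**A short option has its own costs.** A web K10 in the primary analysis would mix self-report with interview, and could do so unevenly by arm. It would also bypass the assessor contact on which section 11 relies. Offered too early, even a short phone call could displace full interviews that later attempts would have secured, and Aim 2 needs the mechanism scales. These points stand and shape the fix.

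**Conclusion.** This is a worthwhile, low-cost improvement to data collection. As written, a reachable participant who declines the battery loses that visit's K10 for want of a stated shorter route, while the phone channel, staff and contacts already exist.

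The benefit is a partial reduction in missing primary outcomes and in reliance on missing at random. Its size is unknown. The movement from about 75% to about 77–80% power with 303 randomised is illustrative. It rests on an assumed recovery of 10% to 25%, a two-group comparison at 0.40 with a two-sided 5% test, and 35% attrition counted as no K10 at all. With 321 randomised the starting point is about 77–78%.

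Two stronger readings are tempting and unsupported. One is that most of the exposure to missing data could be removed this way: nothing in the protocol shows that most missing participants would be reachable and merely unwilling. The other is that the shortfall from 224 is caused by the rebooking rule: at 345 recruited, 35% attrition leaves 224 with no recovery at all.

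**What to change.** Amend the missed-assessment paragraph in section 10.1 as follows:

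- The full interview remains the first offer. When a participant declines it, or at the last of the eight contacts, a blinded assessor offers a K10-only interview by phone. The offer does not come earlier, so that full interviews needed for Aim 2 are not displaced.
- K10 values obtained this way are flagged and included in the primary intention-to-treat mixed model.
- A self-completed online K10, if used at all, is a last resort. Its mode is recorded and it enters a sensitivity analysis only.
- For each missed assessment, record whether the participant was unreachable, declined the full interview, or accepted the K10 only, by arm. This supplies the split that the protocol now lacks.

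The cost is a short amendment and brief assessor training, with the same staff and contacts. The downside is that these calls yield no mechanism or secondary scales.
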